| MPN-SAF TSS (QoL)                                                                                                                           | X                                               |                                                                                                                                     |          |                           | X              |                                      |                                              |
| Administration of tamoxifen                                                                                                                 |                                                 | <<Continuous 20mg once daily from registration>> 
*Consider increasing to 40mg once daily at week 18 if appropriate* |          |                           |                | If clinically indicated              |                                              |
| Blood samples for central review of allele burden                                                                                           | X                                               |                                                                                                                                     | X        |                           | X              | X                        |                                              |
| Bone marrow aspirate and trephine sample
collection                                                                                      |                                                 |                                                                                                                                     |          |                           | X              |                                      |                                              |
| Record of venesections (for PV) or transfusions (for
MF) received                                                                        |                                                 | <<Continuous throughout study>>                                                                                                     |          |                           |                |                                      |                                              |

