#### 7.2.8 Quality of Life

All patients will be required to complete the Myeloproliferative Neoplasm Symptom Assessment Form Total Symptom Score (MPN-SAF TSS) [23] at baseline and week 24 of the study. The questionnaire can be found in Appendix 9. This will be used in order to assess symptom improvement which forms part of the response evaluation. The research team should complete the first page of the booklet prior to providing this to the patient.

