#### 7.2.9 Assessment of response

##### Weeks 2-16

ET and PV patients will be assessed at each protocol scheduled visit for haematological response according to 2009 ELN criteria [1] (Appendix 5) by the Investigator. This will include review of the platelet count, HCT (PV only) and WBC in combination with ultrasound (if applicable) and requirement for venesection. An ultrasound is only applicable prior to 24 weeks if the patient entered the trial in haematological PR with an enlarged spleen on imaging. In these cases, an ultrasound showing a normal spleen must be obtained in order to report haematological CR when this is suspected.

For MF patients, assessment of haematological response will be performed at each protocol scheduled visit using the IWG-MRT criteria [2] (Appendix 6). "Maintenance of response" will be defined as no evidence of disease progression. Disease progression is defined in Appendix 6 but please note a bone marrow to confirm disease progression prior to 24 weeks should only be performed if clinically indicated according to local practice.

---

### Week 24

The trial bone marrow performed at week 24 will be centrally reviewed and a trephine histopathology report issued. Sites will be requested to provide an anonymised report from the latest bone marrow assessment available for each patient prior to registration to ensure a comparison report can be prepared from the trial biopsy at 24 weeks.

Central review of the bone marrow trephine sample will not be fed back in real time and therefore cannot be a guide for patient management.

Sites will then perform the 24 week response assessment upon receipt of this histopathology report using all the relevant clinical data.

For ET and PV patients, assessment of response at 24 weeks will be performed against the 2013 ELN criteria [3] (Appendix 7) using the BM report and results of blood counts (platelets, WBC, haematocrit), blood film, liver/spleen on palpation, symptom assessment (via MPN SAF) and occurrence of haemorrhagic or thrombotic events.

For MF patients, assessment of response at 24 weeks will be performed against IWG-MRT criteria [2] (Appendix 6) using the BM report and results of blood counts (haemoglobin, neutrophils, platelets), blood film for presence of immature myeloid cells and spleen on palpation.

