## APPENDIX 6 – REVISED RESPONSE CRITERIA FOR MYELOFIBROSIS

Ref: Tefferi *et al.* (2013). Revised response criteria for myelofibrosis: International Working Group-Myeloproliferative Neoplasms Research and Treatment (IWG-MRT) and European LeukemiaNet (ELN) consensus report. Blood **122** (8) 1395-1398 [2].

These criteria will be used to assess the endpoints of maintenance of response (no evidence of disease progression) in patients with MF and response assessment at 24 weeks.

| Response categories                                                               | Required criteria (for all response categories, benefit must last for ≥12 wk to qualify as a response)                                                                                                                                                                                                                                                                                                                                                                                                                                                                                                                                                                           |
|-----------------------------------------------------------------------------------|----------------------------------------------------------------------------------------------------------------------------------------------------------------------------------------------------------------------------------------------------------------------------------------------------------------------------------------------------------------------------------------------------------------------------------------------------------------------------------------------------------------------------------------------------------------------------------------------------------------------------------------------------------------------------------|

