| CR                                                                                | Bone marrow:* Age-adjusted normocellularity; <5% blasts; ≤grade 1 MF† and
Peripheral blood: Hemoglobin ≥100 g/L and <UNL; neutrophil count ≥ 1 x 10  /L and <UNL;
Platelet count ≥100 x 10  /L and <UNL; <2% immature myeloid cells‡ and
Clinical: Resolution of disease symptoms; spleen and liver not palpable; no evidence of EMH                                                                                                                                                                                                                                                                                                            |
| PR                                                                                | Peripheral blood: Hemoglobin ≥100 g/L and <UNL; neutrophil count ≥1 x 10  /L and <UNL; platelet count ≥100 x 10  /L and <UNL; <2% immature myeloid cells‡ and
Clinical: Resolution of disease symptoms; spleen and liver not palpable; no evidence of EMH or
Bone marrow:* Age-adjusted normocellularity; ,
<5% blasts; ≤grade 1 MF†, and peripheral blood: Hemoglobin ≥85 but <100 g/L and <UNL; neutrophil count ≥1 x 10  /L and <UNL; platelet count ≥50, but <100 x 10  /L and <UNL; <2% immature myeloid cells‡ and
Clinical: Resolution of disease symptoms; spleen and liver not palpable; no evidence of EMH |
| Clinical Improvement                                                              | The achievement of anemia, spleen or symptoms response without progressive disease or increase in severity of anemia, thrombocytopenia, or neutropenia§                                                                                                                                                                                                                                                                                                                                                                                                                                                                                                                          |

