| Complete Remission                                                                                                                                                                                                                                                                                                                                                                                                                                                                                                                                                                                                                                                                                                                                              |                                                                                                                                                                                     |
| A                                                                                                                                                                                                                                                                                                                                                                                                                                                                                                                                                                                                                                                                                                                                                                      | Durable* resolution of disease-related signs including palpable hepatosplenomegaly, large symptoms improvement,† AND                                                                |

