| 
Molecular response is not required for assignment as complete response or partial response. Molecular response evaluation requires analysis in peripheral blood granulocytes. Complete response is defined as eradication of a pre-existing abnormality. Partial response applies only to patients with at least 20% mutant allele burden at baseline. Partial response is defined as <math>\geq 50\%</math> decrease in allele burden.
 
WBC, white blood cell.
 
*Lasting at least 12 wk.
 
†Large symptom improvement (<math>\geq 10</math>-point decrease) in MPN-SAF TSS.
 
‡For the diagnosis of post-PV myelofibrosis, see the IWG-MRT criteria; for the diagnosis of myelodysplastic syndrome and acute leukemia, see WHO criteria.
 |                                                                                                                                                                                     |

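### The week-24 response criteria ask for 12 weeks of benefit, but the symptom score is measured once after baseline: the conflict is clear for MF, and for ET/PV it depends on an unsettled reading

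*Combined protocol and SAP*

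**What the plan says.** **When the score is taken.** Section 7.2.8 has patients complete the "Total Symptom Score (MPN-SAF TSS) [23] at baseline and week 24 of the study". The Schedule of Events agrees: its questionnaire row is marked at baseline and 24 weeks, and is blank at weeks 4, 12 and 18, beyond week 24, and at the end of study visit.

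**What the score is for.** Section 7.2.8 adds: "This will be used in order to assess symptom improvement which forms part of the response evaluation". For ET and PV, section 7.2.9 lists among the week-24 inputs "symptom assessment (via MPN SAF) and occurrence of haemorrhagic or thrombotic events". Sites make the week-24 assessment once they have the central marrow report.

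**MF criteria (Appendix 6).** The table header states: "for all response categories, benefit must last for ≥12 wk to qualify as a response". CR and PR both need "Resolution of disease symptoms; spleen and liver not palpable; no evidence of EMH". Symptoms response, one route to clinical improvement, is a fall of at least 50% in the score, and the footnote says that symptoms are evaluated with this instrument.

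**ET/PV criteria (Appendix 7).** Criterion A for CR is "Durable* resolution of disease-related signs including palpable hepatosplenomegaly, large symptoms improvement", and PR has nearly the same wording. The asterisk means "Lasting at least 12 wk". The dagger on symptom improvement gives a fall of at least 10 points and no duration.

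**Where it is used.** Sections 2.2 and 12.1.2 list response category at 24 weeks as a secondary outcome. Section 12.2.2 reports numbers and percentages per category.

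**The concern.** A 12-week duration cannot be documented from one reading. Blood counts and palpation are scheduled at weeks 4, 12 and 24, so durability of those components can be checked. The symptom score, which carries the numerical thresholds, has one post-baseline value.

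The protocol does not tell sites what to do about this. One site could hold that durability is unproven and withhold the category. Another could accept the week-24 value alone. Both could say that they followed the protocol, and identical patients would fall in different rows of the same table. The reported CR and PR proportions could then not be described, without qualification, as 2013 ELN or IWG-MRT responses.

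**Working it through.** **Plan's own figure.** The sample size is not an input here, but it was reproduced to confirm that it stands apart from this point. With n = 42 and success at 3 or more responders, the exact binomial gives P(X ≥ 3 | 2%) = 0.0515 (limit 0.10) and P(X ≥ 3 | 10%) = 0.805 (target 0.80). At n = 41 power is 0.791, so 42 is the smallest n that meets both limits. Nothing below alters it.

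**Duration that can be documented by week 24.** This is the last minus the first post-baseline score.

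| Score taken at weeks | Longest documentable benefit | Meets 12 weeks? |
|---|---|---|
| 0, 24 (as planned) | 24 − 24 = 0 | No |
| 0, 18, 24 | 24 − 18 = 6 | No |
| 0, 12, 24 | 24 − 12 = 12 | Yes, on nominal dates |
| 0, 4, 12, 18, 24 | 24 − 4 = 20 | Yes |

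**Can anything else fill the gap?** Most items in Appendix 9 ask about the past 24 hours (weight loss asks about 6 months), so the week-24 form does not cover the preceding 12 weeks. Section 7.2.2 mentions a symptom assessment at weeks 4, 12, 18 and 24, but lists performance status, blood pressure, palpation and weight, and week 18 may be by telephone. It cannot show a 10-point or 50% change in score. No section waives or adapts the 12-week rule.

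**MF.** The rule covers all response categories. A score-based symptoms response therefore cannot be shown to qualify by week 24. Durable symptom resolution for CR and PR has no second score to support it. Anaemia response and spleen response do not use the score, so clinical improvement by those routes remains open. In addition, the MF input list for week 24 in section 7.2.9 names marrow, counts, film and spleen but not symptoms, although Appendix 6 needs them.

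**ET/PV.** There are two readings of criterion A:
- The asterisk governs the whole phrase. Symptom improvement must then last 12 weeks, and no ET/PV patient can be shown to meet CR or PR.
- The asterisk governs signs only. A single week-24 score then decides the symptom component.

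**Patients concerned.** The recruitment minimums are 15 PV, 10 ET and 5 MF. If they are met, ET/PV is 15 + 10 = 25 up to 42 − 5 = 37 patients, and MF is 5 up to 42 − 25 = 17.

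**Illustration for the ELN symptom component only.** The inputs are assumed and are not in the documents: score SD 15, test-retest correlation ρ of 0.7 to 0.9, normal errors, no true change. The SD of change is 15√(2(1 − ρ)), and two changes that share a baseline have correlation 0.5.

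| ρ | SD of change | Fall ≥ 10 at one visit | Fall ≥ 10 at both weeks 12 and 24 |
|---|---|---|---|
| 0.7 | 11.6 | 19% | 8% |
| 0.8 | 9.5 | 15% | 6% |
| 0.9 | 6.7 | 7% | 2% |

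These are chances of passing one component. They are not false-response rates, and they say nothing about the MF 50% threshold.

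**The case against.** The strongest counter-argument concerns Appendix 7. The asterisk sits on resolution of signs, while symptom improvement carries its own footnote, which sets no duration. The PR rows separate the two with a conjunction, and criterion B repeats the asterisk in its own right. On that reading one week-24 score is enough for ET/PV, which is most of the trial. This stands as a legitimate reading. It is not the only one, and the protocol does not choose between them.

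For MF, the footnote naming the instrument is attached to symptoms response, not to the CR and PR rows. A clinician's symptom assessment at weeks 12 and 24, with the other clinical data, might arguably support resolution of symptoms. That has some force for CR and PR. It has none for symptoms response, which is defined by the score.

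A reader might infer that the week-24 table must come out entirely as no response, or that none of the 42 patients can qualify. The documents do not support this. The MF criteria have no such category; patients can be in clinical improvement, stable disease, progressive disease or relapse. Clinical improvement can arise without the score. The ET/PV result depends on the reading, and ET/PV also has a progressive disease category. Nor does a single score decide the whole ET/PV classification, because CR and PR also need durable count remission, absence of progression and of haemorrhagic or thrombotic events, and a marrow finding.

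Finally, this is one of six secondary outcomes, all described as descriptive.

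**Conclusion.** The point holds with limited reach. For MF the schedule and Appendix 6 conflict: 0 of 12 required weeks can be documented for a score-based symptoms response, and CR and PR lack a repeated score for their symptom element. This follows from the documents without any assumption. For ET/PV the finding is an ambiguity that changes the result: CR and PR are either undemonstrable for every such patient or rest, for symptoms, on one reading with mostly 24-hour recall.

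The primary outcome, the rule of 3 or more responders, the 2009 ELN haematological response and the ET/PV improvement outcome do not use the score and are unaffected. The MF part of the improvement outcome relies on Appendix 6 and inherits the problem. The percentages in the illustration depend on the assumed SD and correlation, and the conclusion does not need them. The change should be made, but it does not threaten the trial's main conclusion.

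**What to change.** 1. Add the MPN-SAF TSS to the existing week-12 visit, in the Schedule of Events and section 7.2.8.
2. State in sections 7.2.9 and 12.2.2 that the symptom criterion is confirmed only if its threshold is met at both week 12 and week 24, counting nominal visits. Report patients who meet it at week 24 only as 'not confirmed'.
3. State whether the asterisk in criterion A of Appendix 7 covers symptom improvement as well as signs.
4. Reconcile the MF week-24 input list in section 7.2.9, which omits symptoms, with Appendix 6.

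If the form cannot be added, say that symptoms are judged at week 24 only and label the outcome as modified criteria.

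**Cost.** At most 42 extra one-page questionnaires, at a visit that already includes an examination and blood tests. Symptom improvement that begins after week 12 would be reported as unconfirmed. Sample size and primary analysis do not change.

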#### 7.2.9 Assessment of response

##### Weeks 2-16

ET and PV patients will be assessed at each protocol scheduled visit for haematological response according to 2009 ELN criteria [1] (Appendix 5) by the Investigator. This will include review of the platelet count, HCT (PV only) and WBC in combination with ultrasound (if applicable) and requirement for venesection. An ultrasound is only applicable prior to 24 weeks if the patient entered the trial in haematological PR with an enlarged spleen on imaging. In these cases, an ultrasound showing a normal spleen must be obtained in order to report haematological CR when this is suspected.

For MF patients, assessment of haematological response will be performed at each protocol scheduled visit using the IWG-MRT criteria [2] (Appendix 6). "Maintenance of response" will be defined as no evidence of disease progression. Disease progression is defined in Appendix 6 but please note a bone marrow to confirm disease progression prior to 24 weeks should only be performed if clinically indicated according to local practice.

---

### Week 24

The trial bone marrow performed at week 24 will be centrally reviewed and a trephine histopathology report issued. Sites will be requested to provide an anonymised report from the latest bone marrow assessment available for each patient prior to registration to ensure a comparison report can be prepared from the trial biopsy at 24 weeks.

Central review of the bone marrow trephine sample will not be fed back in real time and therefore cannot be a guide for patient management.

Sites will then perform the 24 week response assessment upon receipt of this histopathology report using all the relevant clinical data.

For ET and PV patients, assessment of response at 24 weeks will be performed against the 2013 ELN criteria [3] (Appendix 7) using the BM report and results of blood counts (platelets, WBC, haematocrit), blood film, liver/spleen on palpation, symptom assessment (via MPN SAF) and occurrence of haemorrhagic or thrombotic events.

For MF patients, assessment of response at 24 weeks will be performed against IWG-MRT criteria [2] (Appendix 6) using the BM report and results of blood counts (haemoglobin, neutrophils, platelets), blood film for presence of immature myeloid cells and spleen on palpation.

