### Sample Size

A total of 42 patients will be recruited over 28 months. Of the 42 patients, we will aim to achieve a minimum of 15 PV patients, 10 ET patients and 5 MF patients.

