### Trial Duration

All patients will receive trial treatment for 24 weeks. Following 24 weeks, they will be able to continue treatment with tamoxifen if there is clinical benefit, at the discretion of the treating Investigator, and their response will be reassessed after 36 and 48 weeks of treatment as applicable. The last patient visit will be 28 days after the last administration of trial treatment.

Recruitment will be over 28 months from 13-15 trial centres. Therefore the total trial duration will be 35 months for patients receiving treatment for 24 weeks. For patients continuing treatment for 36 and 48 weeks, the total trial duration will be 38 and 41 months, respectively.

---

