## 3. TRIAL DESIGN

This is a single arm, open label, multicentre, phase II trial of tamoxifen in patients with MPNs.

The aim of the study is to evaluate the activity of tamoxifen in terms of reducing allele burden and the safety of giving tamoxifen in this group of patients. A single stage A'herns design has been chosen to give evidence of activity for the treatment.

All patients will receive a minimum of 24 weeks of treatment with tamoxifen at 20mg od. Patients will be seen at weeks 4, 12, 18 and 24. Mutant allele burden of JAK2-V617F, CALR 5bp insertion (exon 9) and CALR 52bp deletion (exon 9) will be assessed at baseline. Allele burden will be reassessed at 12 weeks and 24 weeks for the mutation(s) identified at baseline. Patients may continue treatment

beyond 24 weeks at the discretion of the treating Investigator. If patients do continue treatment they should be followed up a minimum of 12 weekly and their allele burden reassessed at 36 weeks and 48 weeks as applicable. All patients will be followed up until 28 days after the last dose of tamoxifen treatment.

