#### 7.2.3 Ultrasound

An ultrasound to assess spleen size will be performed within 6 weeks prior to registration and repeated at 24 weeks. For PV/ET patients entering the trial with PR and enlarged spleen, the

ultrasound at 24 weeks will be performed earlier if a CR is suspected. Thus all patients will have 2 ultrasounds in total. Paper copies of ultrasound results should be posted to the Trial Office upon receipt.

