### **7.3.2 Blood samples**

Peripheral blood samples to allow analysis of JAK2-V617F, CALR 5bp insertion (exon 9) and CALR 52bp deletion (exon 9) mutant allele burden should be collected in lithium heparin tubes and sent to Cambridge at baseline, 12 weeks and 24 weeks.

At baseline and 24 weeks, 60 ml of blood will be collected to allow comparison of oestrogen receptor signalling in progenitor cells.

At week 12, 30 ml blood should be obtained. The remainder of the blood not required to assess allele burden will be banked at CBSB.

The level of allele burden at 12 weeks for each patient will be provided to sites in time to inform a decision about tamoxifen dose escalation and treatment continuation beyond 24 weeks. It is not possible to provide these in real time and therefore they cannot be used as a guide for patient management.

For responder patients continuing treatment beyond 24 weeks and 36 weeks, 60 ml of peripheral blood in lithium heparin tubes should be sent to the CBSB to reassess allele burden at 36 weeks and 48 weeks, respectively. The level of allele burden observed at 24, 36 and 48 weeks for each patient will also be provided to sites to inform a decision about further tamoxifen treatment continuation. It is not possible to provide these in real time and therefore they cannot be used as a guide for patient management.

In the unlikely event that a trial blood sample is lost, damaged or mishandled so it cannot be analysed, the trial office will request another sample.

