## 9. DATA HANDLING AND RECORD KEEPING

### 9.1 Data Collection

The electronic Case Report Form (eCRF) will comprise, but is not limited to, the following forms:

| Form                  | Summary of data recorded    | Schedule for submission         |
|-----------------------|-----------------------------|---------------------------------|
| Eligibility Checklist | Confirmation of eligibility | Completed prior to registration |

|                                       |                                                                                                                                       |                                                  |
|---------------------------------------|---------------------------------------------------------------------------------------------------------------------------------------|--------------------------------------------------|
| Registration                          | Patient details                                                                                                                       | Completed as part of registration                |
| Baseline                              | Medical history, previous treatment, baseline characteristics, haematology/biochemistry assessments and details of medical exam       | Within 2 weeks of registration                   |
| Treatment Form                        | Treatment details, haematology/biochemistry assessments and details of medical exam                                                   | Within 2 weeks of scheduled visit                |
| Treatment Form – Week 24              | Treatment details, haematology/biochemistry assessments, details of medical exam and bone marrow assessment                           | Within 2 weeks of scheduled visit                |
| 28 Days post Treatment Follow-up Form | Haematology/biochemistry assessments, details of medical exam                                                                         | Within 2 weeks of scheduled visit                |
| Adverse Event Form                    | Details of AEs experienced                                                                                                            | Continuous                                       |
| Concomitant Medication Form           | Details of concomitant medications received                                                                                           | Continuous                                       |

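### In ET and PV, 2009 ELN haematological response is graded by open-label sites averaging about three patients, with no central derivation or check, although the inputs it needs are collected

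*Combined protocol and SAP*

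**What the plan says.** Section 3 describes the design: "This is a single arm, open label, multicentre, phase II trial of tamoxifen in patients with MPNs". The synopsis gives the size, "A total of 42 patients will be recruited over 28 months", with a target of "a minimum of 15 PV patients, 10 ET patients and 5 MF patients", and under Trial Duration the number of centres: "Recruitment will be over 28 months from 13-15 trial centres".

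Section 7.2.9 covers response assessment in two blocks.

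- **The block headed Weeks 2-16.** The Investigator grades ET and PV patients by 2009 ELN (Appendix 5) at each scheduled visit. MF patients are graded by IWG-MRT (Appendix 6), with no assessor named.
- **The Week 24 block.** The trephine is reviewed centrally, and then: "Sites will then perform the 24 week response assessment upon receipt of this histopathology report using all the relevant clinical data". The criteria named there are 2013 ELN (Appendix 7) for ET/PV and IWG-MRT for MF.

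Section 12.1.2 uses 2009 ELN in ET/PV for two secondary outcomes. One is haematological response at weeks 12 and 24, limited to patients who enter in CR or PR. The other is improvement in category from baseline to week 24. Section 12.2.2 calls the secondary outcomes descriptive, although it also plans a χ² or Fisher comparison of haematological response.

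On data flow, the week-24 form in section 9.1 holds "Treatment details, haematology/biochemistry assessments, details of medical exam and bone marrow assessment", and section 7.2.3 adds: "Paper copies of ultrasound results should be posted to the Trial Office upon receipt".

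**The concern.** Two reported outcomes rest on a grade given by an assessor who knows that every patient is on tamoxifen. There is no control arm in which the same grading tendency would appear and cancel. Each site grades so few patients that it gains little practice with the rules.

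The rules are easy to mix up. At week 24 an ET/PV patient falls under both ELN sets. The white cell limit for complete response is at most 10 × 10⁹/L in 2009 ELN but below 10 in 2013 ELN. The spleen is judged on imaging in the first and by palpation in the second.

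The grade also has local uses: improvement of haematological response appears in the continuation guidance (7.1) and in the dose modification text (7.4). For 2009 ELN this discretion is avoidable, because the definition consists of numeric cut-offs, a venesection history and an imaging result. What is at stake is how uniform and credible the two outcomes are, not the trial's decision.

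**Working it through.** **1. The plan's own figure, and whether this point touches it.** Inputs from section 12.6: p0 = 0.02, p1 = 0.10, one-sided alpha 0.10, power 80%, success if 3 or more respond. Exact binomial with n = 42:

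- P(X ≥ 3 | 0.02) = 0.0515, within 0.10.
- P(X ≥ 3 | 0.10) = 0.805, above 0.80.
- n = 41 with 3 responders gives power 0.791, and n = 29 with 2 gives alpha 0.114. The smallest design is n = 42 with 3, so the stated 42 is reproduced.

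The primary outcome is a central laboratory measurement (12.1.1). No response category enters it, so these figures do not change.

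**2. Patients per site.** 42/13 = 3.2, 42/14 = 3.0 and 42/15 = 2.8. For ET and PV alone, the minimum targets give at least 15 + 10 = 25 patients, and reserving 5 for MF leaves at most 42 − 5 = 37. The average is then between 25/15 = 1.7 and 37/13 = 2.8 per site.

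**3. Can 2009 ELN be derived from what is collected?**

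| Appendix 5 input | Source | Rule needed |
|---|---|---|
| Platelets, white cells | 7.2.4: baseline, weeks 12 and 24 | none |
| Haematocrit (PV) | 7.2.4: same visits | none |
| No venesection for 3 months (PV) | Schedule of Events: recorded throughout the study | count for the 3 months before registration (4.1 already requires the site to look back over this period) |
| Normal spleen on imaging | 7.2.3: ultrasound at baseline and week 24, earlier if CR is suspected in a patient entering in PR with an enlarged spleen | use of the latest available imaging |

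It can, given those two rules and entry of the paper ultrasound reports.

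**4. Can the other two sets be derived?** Not in full.

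- 2013 ELN (symptom improvement) and IWG-MRT (all responses) require benefit lasting 12 weeks. MPN-SAF is completed only at baseline and week 24 (7.2.8), so a lasting symptom change cannot be shown by a site or by a program.
- In MF, spleen response and splenic progression need MRI or CT. Absence of extramedullary haematopoiesis refers to pathology or imaging. Neither is scheduled for these purposes.
- The form list in 9.1 names no MPN-SAF form, although that list is not exhaustive.

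**5. Sensitivity of the results.** One regraded patient moves a proportion by 1/n: 1/42 = 2.4 points, 1/37 = 2.7, 1/25 = 4.0, 1/15 = 6.7 (PV minimum), 1/10 = 10 (ET minimum). The haematological-response denominator is smaller if some patients do not enter in CR or PR. All eligible ET patients do enter in at least PR, since 4.1 requires platelets of at most 600 × 10⁹/L and Appendix 5 sets PR at that level. PV patients need not.

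**6. Illustration under an assumption.** The documents give no rate of disagreement between a site and a derived category. If it were 5%, 10% or 20%, then among 25 to 37 ET/PV patients about 1.3 to 1.9, 2.5 to 3.7, or 5.0 to 7.4 would change category. Changes in opposite directions would partly cancel. For scale, the exact 95% interval for 21/42 is 34% to 66%.

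**7. Who assigns what.** Section 7.2.7 says the marrow is assessed centrally for response, while 7.2.9 gives the week-24 assessment to sites. The Week 24 block names no assessor for the 2009 ELN grade that 12.1.2 needs then. The heading Weeks 2-16 does not match the visits at weeks 4, 12, 18 and 24. For MF, the week-24 input list in 7.2.9 omits the liver and symptoms, both of which Appendix 6 requires for CR and PR.

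**The case against.** The strongest case against is that this is a refinement of secondary outcomes declared descriptive, while the primary outcome and the rule of 3 or more responders rest on a central assay. If the criteria are mostly numeric, site discretion is small to begin with. Histology, the most interpretive component, is already read centrally. A patient who enters in PR with an enlarged spleen cannot be reported in CR without an ultrasound showing a normal spleen. Section 10.3 has trial staff check forms for compliance and consistency. All of this stands and keeps the point minor. But those checks do not re-derive a category, and numeric criteria are exactly the ones that are cheap to compute once.

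Four stronger readings are tempting, and the documents do not support them.

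- *One program could derive every response category.* Step 4 shows that it could not for 2013 ELN or IWG-MRT.
- *Graders know the molecular result.* The plan does say "The level of allele burden at 12 weeks for each patient will be provided to sites", but section 7.3.2 adds that results are not available in real time. The week-12 grade belongs to the visit at which that sample is drawn, so it normally precedes the result. At week 24 the week-12 result will normally be known. Whether the week-24 result arrives before grading is not stated.
- *Sites must record improvement for treatment to continue.* Section 7.1 encourages continuation without mandating it, lists other qualifying criteria, and leaves the choice to the Investigator.
- *Reported response will be inflated.* With no disagreement rate in the documents, neither the direction nor the size can be given.

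**Conclusion.** The point holds for 2009 ELN in ET and PV. Unblinded local grading at sites averaging 2.8 to 3.2 patients (all diseases), with no central derivation or check, produces a category that could be computed the same way for everyone. It affects two secondary outcomes. One regraded patient is worth 2.4 points in all 42, and 6.7 (PV) or 10 points (ET) at the planned minimum numbers.

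This rests on two readings. One is that the Investigator's role in 7.2.9 extends to the 2009 ELN grade at week 24, which the text does not say outright. The other is that venesection counts and ultrasound findings can be put into analysable form. Sample size, error rates and the go/no-go rule are unchanged. It is a cheap improvement, not a flaw that threatens the trial.

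**What to change.** 1. In 12.2.2, state that the ET/PV 2009 ELN analysis category at baseline, week 12 and week 24 is derived by program at the Trials Office from eCRF values and ultrasound reports. Give the rule for using the latest available spleen imaging and for counting venesections over the preceding 3 months, including before registration.
2. Keep the site's category for local use, report it as a sensitivity analysis, and tabulate disagreements by disease and visit.
3. For 2013 ELN and IWG-MRT, limit the program to a consistency check of the derivable components. State how unobservable 12-week symptom durability and missing MRI/CT are handled.
4. Reconcile 7.2.7 with 7.2.9 on who assigns response, name the assessor of the week-24 2009 ELN grade, correct the heading Weeks 2-16, and align the MF input list in 7.2.9 with Appendix 6.

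The cost is programming time, entry of paper ultrasound reports and some data queries. It needs no extra visits, readers or procedures. The drawback is that some derived categories will differ from the site's and must be shown.
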